### Data collection method

a) From professionals: the collection of socio-demographic data on the health professionals and the completion of the questionnaire on breastfeeding knowledge will take place before the start of any other activity.

b) From mothers: The inclusion of mothers in the study will take place on the infant's first consultation at the PHCC. The nurse and/or paediatrician will inform the mother and request her consent.

The collection of information about the breastfeeding will be by telephone interview, undertaken by an individual interviewer trained for the purpose; who does not know to which group the woman belongs.

Phonecalls will be scheduled at 1, 3, 6 and 12 months from the beginning of the study. During each call the mother will be asked if the infant is being breastfed at that time and, if the answer is negative, will be asked the date breastfeeding ceased and the reason for stopping. Each woman will be followed for a period of 12 months from the child's birth or until the time when breastfeeding ceases.

The timing of collection of data on the different variables is shown in Figure 1, in which the project structure and the data collection procedure are shown.

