**Method/Design:**

This study involves a community based cluster randomized trial in primary healthcare centres in Leganés (Madrid, Spain). The project aims to determine whether the use of an implementation strategy (including training session, information distribution, opinion leader) of a breastfeeding guideline in primary care is more effective than usual diffusion.

The number of patients required will be 240 (120 in each arm). It will be included all the mothers of infants born during the study period (6 months) who come to the health centre on the first visit of the child care programme and who give their consent to participate. The main outcome variable is the exclusive o predominant breastfeeding at 6 moths of age..

Main effectiveness will be analyzed by comparing the percentage of infants with exclusive or predominant breastfeeding at 6 months between the intervention group and the control group. All statistical tests will be performed with intention to treat. Logistic regression with random effects will be used to adjust for prognostic factors. Confounding factors or factors that might alter the effect recorded will be taken into account in this analysis.

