## Background

### Current breastfeeding situation

The World Health Organization (WHO) considers breastfeeding the ideal way to feed infants, as it provides them with the nutrients needed for adequate growth and development, recommending exclusive breastfeeding until 6 months [1] and its continuance in supplemented form until 2 years of age [2].

Nowadays efforts are being made in both health and non-health areas for promoting the initiation and continuation of breastfeeding. Its benefits as much to the mother as to the infant, are widely known and it is thought to be an important factor in the promotion of children's health [3-6]. In spite of this, breastfeeding statistics are far from the levels considered adequate by the WHO, which estimates that 97% of women of fertile age are able to breastfeed their children.

In the latest *The State of the World's Children Report*, published in 2007 by the United Nations Children's Fund (UNICEF), it is noted that breastfeeding figures in Europe are discouraging (22% exclusive breastfeeding in infants less than 6 months old) [7]. In our country there is no official record system to make available data on the tracking and monitoring of breastfeeding. According to information from the latest *National Survey of Health*, in Spain breastfeeding at 6 months of age is 24.72% and in Madrid 23.54% [8]. In the study undertaken by the Spanish Paediatrics Association it is concluded that the average length of breastfeeding in Spain is about 3 months and only 24.8% of infants are breastfed at 6 months of age [9]. The data which has been obtained from existing records of computerised health reports in Primary Healthcare centres (PHCC) in our city show us a rather more unfavourable panorama as the percentage of 18.26%.

The WHO enumerated "*Ten Steps Towards Happy and Natural Breastfeeding" *[10] which are the basis for the introduction of projects based on the Baby Friendly Hospital Initiative (BFHI) which establishes an integrated approach to increase breastfeeding and has shown very positive results according to some studies [11,12].

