### Subjects of the study

Mother of infants born between 1st June 2010 and 1st December 2010 who came to the PHCC on the first visit of the Child Care Programme.

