### Variables

#### Outcome variables

The main outcome variable is the mother-infant pairs using EBF o PBF at six months

The secondary outcome variables will be:

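### The telephone calls are timed from the start of the study rather than from birth, which conflicts with a primary outcome at 6 months of age and on the plausible reading makes the 6-month call late

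*Protocol article*

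**What the plan says.** Three time origins appear in the protocol article.

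- **Calls.** Data collection method: "Phonecalls will be scheduled at 1, 3, 6 and 12 months from the beginning of the study". The start of the study is not defined there or elsewhere in the text.
- **Primary outcome.** Abstract, Method/Design: "The main outcome variable is the exclusive o predominant breastfeeding at 6 moths of age". The Sample size section also sets its target difference on feeding at 6 months of age. The Outcome variables section gives no origin: "The main outcome variable is the mother-infant pairs using EBF o PBF at six months".
- **Follow-up.** Data collection method, same paragraph as the calls: "Each woman will be followed for a period of 12 months from the child's birth or until the time when breastfeeding ceases".

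On entry, Subjects of the study gives a six-month birth window, "Mother of infants born between 1st June 2010 and 1st December 2010", and Data collection method adds "The inclusion of mothers in the study will take place on the infant's first consultation at the PHCC". The infant's age at that consultation is not stated.

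Each call asks whether the infant is being breastfed at that moment and, if not, when and why breastfeeding stopped. Mother-infant pair variables lists the birth date, EBF or PBF status if breastfed, and the date and reason of stopping if not.

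**The concern.** The primary outcome is a status at a fixed age, so the age at which the call is made determines what is measured. A call schedule with a different origin from the endpoint is a stated rule that conflicts with it, not a detail left to a fuller document.

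The chosen age makes the timing matter. The Background cites the WHO as "recommending exclusive breastfeeding until 6 months [1] and its continuance in supplemented form until 2 years of age". A mother who follows that advice changes from exclusive to supplemented feeding at about the age the endpoint is meant to capture. A call made some weeks later sees her after the change, and the error runs one way: an infant who was EBF/PBF at 6 months can be counted as not. The planned comparison of 38% with 18% would then be made on lower percentages and, other things equal, with a smaller absolute difference.

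**Working it through.** **1. The plan's own figure.** With 18% against 38%, two-sided alpha 0.05, 80% power and a continuity correction, the requirement is 88 per arm, or 176, as stated. Design effect: 1 + (30 − 1) × 0.01 = 1.29. Then 176 × 1.29 / 0.95 = 239.0, against the stated 240. The size reproduces, and the call origin does not enter it.

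**2. Age at the 6-month call under each reading of the origin.**

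(a) *One calendar date.* The document gives no study start date, so take the first day of the birth window, 1 June 2010, as an assumption. The window to 1 December 2010 is 183 days.
- 1-month call, 1 July: 30/183 = 16% of the window has passed.
- 3-month call, 1 September: 92/183 = 50% has passed.
- 6-month call, 1 December: infants are 0 to 6 months old.

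Most infants would be unborn at the first call and about half at the second. This cannot be what is meant.

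(b) *Each mother's inclusion.* Age at the call = 6 months + age at first consultation. That age is not given; assuming 3 to 30 days and 30.44 days per month:

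| Age at first visit (assumed) | Age at 6-month call |
|---|---|
| 3 days | 6 + 3/30.44 = 6.1 months |
| 7 days | 6 + 7/30.44 = 6.2 months |
| 15 days | 6 + 15/30.44 = 6.5 months |
| 30 days | 6 + 30/30.44 = 7.0 months |

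Every call is late and none is early. The 12-month call would similarly fall at about 12.1 to 13.0 months, after the stated end of follow-up at 12 months from birth.

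(c) *Birth.* The call falls at 6 months of age for every infant. This matches the endpoint but is not what the call sentence says.

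**3. Can the recorded fields recover status at 6 months of age after a late call?**
- Infant weaned between 6 months and the call: birth date and cessation date show that the infant was still breastfed at 6 months, but not whether exclusively or predominantly.
- Infant changed from EBF/PBF to partial feeding between 6 months and the call: still breastfed, so no date is asked.

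The fields recover any breastfeeding at 6 months, not the primary outcome.

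**4. Illustration of the consequence.** Suppose a fraction f of infants who are EBF/PBF at 6 months are supplemented by the time of the call, with f equal in both arms. The document gives no f. Take n = 88 per arm, before clustering, and d = p2 − p1. The continuity-corrected size is n' = (n − 1/d)² / n, and z = [d√n' − 1.96√(2p̄(1 − p̄))] / √(p1(1 − p1) + p2(1 − p2)). At f = 0, n' = (88 − 5)²/88 = 78.3 and z = 0.85, giving 80%, as planned.

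| f (assumed) | Control | Intervention | Power |
|---|---|---|---|
| 0 | 18.0% | 38.0% | 80% |
| 0.1 | 16.2% | 34.2% | 74% |
| 0.2 | 14.4% | 30.4% | 66% |
| 0.3 | 12.6% | 26.6% | 58% |

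This shows direction and sensitivity only; it is not an estimate for this trial.

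**The case against.** The best defence is that the call sentence is loose wording. The paragraph goes on to count follow-up from birth, and a 12-month call fits inside 12 months from birth only if calls are also counted from birth. Figure 1, said to show when each variable is collected, is not visible and may state the origin. This stands as a reason for moderate confidence. It does not make the sentence correct, and staff who schedule calls by it would not be using infant age.

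It is also fair that the cessation date is recorded, so the call does more than take current status, and that a survival analysis of the duration of each type of breastfeeding is planned, which would need a date for the end of EBF/PBF. But neither Mother-infant pair variables nor Data collection method mentions such a date.

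The recommendation to supplement after 6 months describes advice, not behaviour. The article reports no observed fall at that age and puts mean breastfeeding duration in Spain at about 3 months. That stands: the size of the effect is unknown.

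A reader might infer three stronger points that the document does not support:
- *The outcome is taken at 0 to 6 months of age.* This needs the calendar reading, under which many calls precede birth.
- *The rates are driven towards zero.* Only a downward direction can be argued.
- *The arms are biased against each other.* One schedule applies to both, the interviewer does not know the group, and nothing suggests that first-visit age differs by arm.

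**Conclusion.** The stated origin of the calls conflicts with the age-based primary outcome and with follow-up from birth in the same paragraph, and the passages must be reconciled. On the plausible reading, inclusion at the first consultation, every 6-month call is late by the infant's age at that visit: about 0.1 to 1.0 month if that age is 3 to 30 days, which is an assumption. A late call can turn a true EBF/PBF case at 6 months into a non-case, and the fields described cannot reverse that. The effect on the two percentages is downward and its size cannot be computed from the document. It is not shown that calls were in fact made late, and Figure 1 may settle the intended origin. This is an inconsistency worth correcting because it touches the primary endpoint, not a demonstrated mistiming.

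**What to change.** - State that all calls, at 1, 3, 6 and 12 months, are timed from the infant's date of birth, which is already recorded.
- At the 6-month call, ask for feeding status on the day the infant reached 6 months and, if the infant is no longer EBF/PBF, the date of first supplementation.
- Analyse status at 6 months of age whatever the date of the call, and give the same origin in the Outcome variables section, which now has none.
- Check that Figure 1 shows the same origin.

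The cost is one reworded sentence in Data collection method and one added question. It needs no extra calls, and the sample size of 240 is unchanged. The added date would also serve the planned analysis of the duration of EBF and PBF. The answer depends on recall, but over a short interval if the call is made close to 6 months of age.

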**Figure 1 F1:**
[figure not shown]
**Project structure**.

### Statistical Analysis

The use of randomisation by clusters conditions the statistical analysis that can be employed, especially in the calculation of confidence intervals and the testing of hypotheses. The following analyses will be undertaken:

Descriptive analysis of each variable with its corresponding CI at 95%. Description of the profile of patients who abandon the study plus their reason for withdrawal.

Comparison of the group at the beginning of the trial with regards to response variables, descriptive variables, and prediction factors. Bivariate statistical tests will be used suitable to the type of variable (qualitative or quantitative).

Analysis of primary outcome. There will be a comparison of the percentage of infants using EBF or PBF at 6 months in the two study arm using the Chi-squared test and the calculation of confidence intervals.

Logistic regression with random effects will be used to adjust for prognostic factors. Confounding factors or factors that might alter the effect recorded will be taken into account in this analysis.

To assess the effect of the intervention on the duration of the various types of breastfeeding, a survival analysis will be used comparing the two groups using the log-rank test. The control of potential confounding variables will be performed by the construction of various Cox regression models.

Effect of the intervention on secondary outcome variables: comparison of the proportion the percentage of EBF or PBF at 1, 3 and 12 months using the Chi-squared test and the calculation of confidence intervals.

All statistical tests will be performed with intention to treat. The last observation carried forward will be used for missing data. Significance will be set at P < 0.05. All calculations will be made using SPSS^© ^v.18 software.

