## Hypothesis

The implementation of a breastfeeding guideline, with the additional support of training and information directed at the professionals who impart the care, implies a greater integration of the guide's recommendations in usual clinical practice. As a result of this integration, an increase in the percentage of breastfed infants and a greater duration of breastfeeding will be produced.

The proportion of infants using exclusive breastfeeding (EBF) or predominant breastfeeding (PBF) at six months will increase at least 20% with respect to the control group (38% for the intervention group compared with 18% for the control group).

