### Sample size

For an alpha of 0.05, a power of 80%, and in order to detect an increase of 20% in the percentage of exclusive or preferential breastfeeding at 6 months of age in the intervention group, the overall sample size required is 176 patients (88 in each arm of the study).

Since randomisation is by clusters, the sample size has to be larger than if simple randomisation is performed, in order to take into account the design effect. The intra-class correlation coefficient is 0.01 [30] and a mean cluster size is assumed to be 30 patients. The design effect is 1.29. Given these assumptions, and expecting a 5% loss rate at one year, the final sample size required is 240 (120 patients in each arm).

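### The primary outcome is tested with a chi-squared test on individual mother-infant pairs although nine health centres are randomised, so the true error rate is above 5%

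*Protocol article*

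**What the plan says.** Under Design of the study and Randomisation, the protocol article allocates nine PHCCs as clusters and takes the mother-infant pair as the unit of analysis. The Sample size section assumes an ICC of 0.01 and a mean cluster size of 30, and states: "The design effect is 1.29".

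The Statistical Analysis section opens by acknowledging the design: "The use of randomisation by clusters conditions the statistical analysis that can be employed". It then names these methods:

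- Primary outcome at 6 months: "comparison of the percentage of infants using EBF or PBF at 6 months in the two study arm using the Chi-squared test", together with confidence intervals.
- Secondary proportions: "comparison of the proportion the percentage of EBF or PBF at 1, 3 and 12 months using the Chi-squared test", again with confidence intervals.
- Duration of breastfeeding: "a survival analysis will be used comparing the two groups using the log-rank test", followed by Cox models for confounders.
- Threshold: "Significance will be set at P < 0.05".

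None of these tests is described as adjusted for centre. Random effects appear once, in a logistic regression whose stated purpose is adjustment for prognostic factors. The section does not say that PHCC is the random effect, nor that this model decides the trial.

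**The concern.** Pairs from one centre share professionals, catchment and advice, so their outcomes are correlated. All pairs in a centre also receive the same allocation. The variance of the difference between arms is therefore larger than a chi-squared test assumes, by roughly the design effect. The plan buys extra patients to cover this inflation and then leaves it out of the test that is meant to decide the result.

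The error runs towards false positives. An ordinary difference between centres can be reported as an effect of the implementation strategy, with a p-value that is too small and an interval that is too narrow.

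This is not a detail that an article leaves to a fuller document. The article names a specific test that does not fit the design, and a later analysis plan could repair this only by contradicting it.

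**Working it through.** **Inputs.** 18% control and 38% intervention (Hypothesis); alpha 0.05, power 80%, ICC 0.01, cluster size 30, 5% loss, 240 pairs (Sample size); nine PHCCs (Randomisation). Assumptions made here: a two-sided test and a 4:5 split of the centres.

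**The plan's own sample size reproduces.** With a mean proportion of 0.28:

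- n = [1.96·√(2·0.28·0.72) + 0.842·√(0.18·0.82 + 0.38·0.62)]² / 0.20² = 77.9 per arm, or 78.
- With continuity correction: (77.9/4)·[1 + √(1 + 4/(77.9·0.20))]² = 87.6, or 88 per arm and 176 in total, as stated.
- Design effect: 1 + (30 − 1)·0.01 = 1.29, as stated.
- 176·1.29 = 227.04, and 227.04/0.95 = 239, stated as 240.

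**Size of the unadjusted test.** If the true variance is DE times the assumed one, a nominal 5% test has size 2·[1 − Φ(1.96/√DE)]. At ICC 0.01:

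| Pairs per PHCC | DE | √DE | True size | Coverage of unadjusted 95% CI |
|---|---|---|---|---|
| 30 (protocol) | 1.290 | 1.136 | 8.4% | 91.6% |
| 240/9 = 26.7 | 1.257 | 1.121 | 8.0% | 92.0% |
| 228/9 = 25.3 (after 5% loss) | 1.243 | 1.115 | 7.9% | 92.1% |

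**Simulation.** Beta-binomial data, 18% in both arms, 4 versus 5 PHCCs, 26 pairs each, 40,000 trials per setting. ICCs other than 0.01 are assumptions.

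| ICC | Chi-squared test, type I error |
|---|---|
| 0.01 (protocol) | 8.1% |
| 0.02 | 11.2% |
| 0.05 | 19.7% |

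A separate run with 27 pairs per PHCC and 100,000 trials gave 8.4% at ICC 0.01.

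**Larger centres.** The Abstract says all mothers of infants born in the six months will be included, so centres could exceed 27 pairs. The documents give no birth counts, so the sizes below are assumptions. At ICC 0.01 the error is about 10.8% at 50 pairs per centre, 16–17% at 100 and 19% at 125.

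**A valid analysis.** Nine centres in two arms leave 9 − 2 = 7 degrees of freedom, with critical value 2.365 instead of 1.96.

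- A t-test on the nine centre percentages has a simulated size of 5.0% at ICC 0.01, and 4.8% when centre sizes vary from 10 to 50.
- The same statistic judged against 1.96 has about 9%. Hence a random-effects model with normal critical values would not be enough.
- Interval width relative to the unadjusted one: √1.243·2.365/1.96 = 1.35 after loss, and √1.29·2.365/1.96 = 1.37 at the protocol's design effect.

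**Power of that analysis at ICC 0.01.**

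- 120 per arm: SE = √[(0.1476 + 0.2356)/120·1.257] = 0.0633 and 0.20/0.0633 = 3.16. On a noncentral t with 7 degrees of freedom, power is about 77%.
- 114 per arm: SE = √[(0.1476 + 0.2356)/114·1.243] = 0.0646 and 0.20/0.0646 = 3.09, giving about 76%.

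**Duration.** The log-rank and Cox analyses are too liberal for the same reason. The amount cannot be computed, because no ICC for duration is given.

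**The case against.** The strongest defence is that a clustered analysis is already planned. The random-effects logistic regression follows directly after the primary comparison, and the Abstract describes the main analysis without naming the chi-squared test. On that reading the fault is unclear precedence. It does not hold up: the chi-squared test is the only one listed under the primary outcome, the model is described as prognostic adjustment, PHCC is not named as its random effect, and duration has no counterpart. At best there are two competing p-values, one of them invalid, and no rule for choosing between them.

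A second defence is that the inflation is moderate at the stated ICC. The 88 per arm reproduces only with a continuity correction. If the test itself were corrected, its size would be about 5.8% at ICC 0.01. That is true, but the plan names no correction for the test, and the corrected version still reaches 8.6% at ICC 0.02, 16.0% at 0.05, and 14.5% with 100 pairs per centre at ICC 0.01.

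Three limits stand:

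- No interval method is specified. That the intervals are unadjusted is inferred from their pairing with the chi-squared test.
- Only the figure of about 8% rests on the protocol's own inputs. Higher figures need a larger ICC or larger centres.
- The remark on normal critical values is conditional, since the article does not say how the random-effects model would be tested.

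**Conclusion.** The point holds, and the section is wrong as written. On the protocol's own ICC of 0.01, the named primary test has a type I error of about 8% at a nominal 5%. Unadjusted 95% intervals would cover about 92% and should be about 1.35 times as wide. This assumes an uncorrected two-sided chi-squared test and roughly equal centres of 26 to 30 pairs. The error grows quickly if the ICC or the centre size is larger than planned, to about 20% at ICC 0.05. The chi-squared tests at 1, 3 and 12 months and the duration analyses share the defect but serve secondary objectives. This must be corrected before the analysis, because it affects the p-value that decides the trial.

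**What to change.** Replace the chi-squared test as the primary analysis and state that one cluster-valid analysis is decisive. Two options are sound:

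- Compare the nine PHCC percentages with a two-sample t-test on 7 degrees of freedom, and take the confidence interval from it.
- Make the logistic model primary, name PHCC as the random effect, and use a small-sample (7 df) or permutation reference. This is closest to the existing text.

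Use the same method at 1, 3 and 12 months. For duration, replace the plain log-rank and Cox analyses with a Cox model with PHCC frailty plus a permutation test over centre allocations, or with a comparison of centre-level summaries. Any permutation set must match the allocation scheme actually used, since the simple random sequence described does not guarantee a 4:5 split.

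The cost is a rewritten analysis section and some programming. The t-test runs in any package, but it should be checked whether SPSS v.18, the only software named, can fit the frailty model and run the permutation test. Intervals widen, and power at the planned size and ICC 0.01 is about 77%, or about 76% after the 5% loss, against the stated 80%. The revised plan should report that figure.

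### Last observation carried forward scores mothers lost while exclusively or predominantly breastfeeding as 6-month successes; it overstates each arm's rate and can shift the comparison either way

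*Protocol article*

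**What the plan says.** The Statistical Analysis section states "All statistical tests will be performed with intention to treat" and then "The last observation carried forward will be used for missing data". It makes no exception for the primary outcome and names no other rule for missing values.

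Under Outcome variables: "The main outcome variable is the mother-infant pairs using EBF o PBF at six months". Under Data collection method: "Phonecalls will be scheduled at 1, 3, 6 and 12 months from the beginning of the study". The same section adds: "Each woman will be followed for a period of 12 months from the child's birth or until the time when breastfeeding ceases". At each call a mother who is no longer breastfeeding is asked when she stopped and why.

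On how the outcome moves with age, the Background cites a national study putting the "average length of breastfeeding in Spain is about 3 months and only 24.8% of infants are breastfed at 6 months of age". The Hypothesis section expects "38% for the intervention group compared with 18% for the control group" at 6 months. The Objectives and Statistical Analysis sections also plan a comparison of EBF/PBF at 12 months. The Sample size section expects 5% loss at one year.

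**The concern.** Carrying the last value forward assumes that no mother changes her feeding after the last contact. For this outcome the assumption fails in one direction. Exclusive or predominant feeding, once ended, is not normally resumed, so a status carried from month 1 or 3 can overstate the 6-month status but hardly understate it. Carrying forward a known cessation does no harm; the fault lies in carrying forward a positive status.

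Follow-up ends when breastfeeding ceases, so the mothers still being called, and hence able to be lost, are those still breastfeeding in some form. The rule therefore acts largely on the mothers for whom it is least safe.

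At stake are the two reported 6-month rates, the difference between them if losses are unequal, and the standard error, because each filled-in value is treated as if it had been observed. The 12-month comparison has the same fault: a status reported months earlier is carried to an age at which, by the feeding recommendation in the Background, infants would be on supplemented feeding.

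**Working it through.** **The plan's own figures.** The loss rate comes from the sample size calculation, which reproduces. For 18% v 38%, two-sided alpha 0.05, 80% power and a continuity correction, n is 88 per arm. The design effect is 1 + (30 − 1) × 0.01 = 1.29. Then 88 × 1.29 = 113.52, and 113.52 / 0.95 = 119.5, so 120 per arm and 240 in all. A 5% loss is 0.05 × 120 = 6 mothers per arm, and each mother wrongly counted as a success adds 1/120 = 0.83 points to her arm.

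**Inputs for the bias.**
- p, the true 6-month EBF/PBF rate: 18% control, 38% intervention (Hypothesis).
- L, the share lost before the 6-month call: 5%. The article gives this for one year, so at 6 months it should be no higher. A 10% loss is used below only to illustrate imbalance.
- q, the share of lost mothers with EBF/PBF at their last call: not in the article; assumed 40–60%.
- Lost mothers are assumed to have their arm's true rate p.

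**Formula.** The expected rate under the rule is (1 − L)p + Lq, so the bias in an arm is L(q − p).

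**Each arm at 5% loss.**
- p = 18%: 0.05 × (0.40 − 0.18) = 1.1 points, to 0.05 × (0.60 − 0.18) = 2.1 points.
- p = 38%: 0.05 × (0.40 − 0.38) = 0.1 points, to 0.05 × (0.60 − 0.38) = 1.1 points.

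**Difference with equal loss and equal q.** 0.05 × (q − 0.38) − 0.05 × (q − 0.18) = 0.05 × (0.18 − 0.38) = −1.0 point, whatever q is. The expected 20 points become 19. If q is 20 points higher in the intervention arm, the shift is zero.

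**Difference with unequal loss** (bias in intervention minus bias in control):

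| Scenario | q = 40% | q = 50% | q = 60% |
|---|---|---|---|
| No true effect (18% in both), 5% control v 10% intervention: (0.10 − 0.05)(q − 0.18) | +1.1 | +1.6 | +2.1 |
| 18% v 38%, 5% control v 10% intervention: 0.10(q − 0.38) − 0.05(q − 0.18) | −0.9 | −0.4 | +0.1 |
| 18% v 38%, 10% control v 5% intervention: 0.05(q − 0.38) − 0.10(q − 0.18) | −2.1 | −2.6 | −3.1 |

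With no true effect the arm with more losses gains, whichever arm that is. At the design rates the sign depends on q and on where the losses fall.

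**A less favourable assumption about who is lost.** Suppose every lost control mother had EBF/PBF at the 3-month call, and 40–60% of the arm did so then. Her chance of still doing so at 6 months would be 18/60 = 30% to 18/40 = 45%. The excess at 5% loss would be 0.05 × (1 − 0.45) = 2.8 points to 0.05 × (1 − 0.30) = 3.5 points.

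**The case against.** The best defence is that the rule does little at the planned loss. About 12 of 240 mothers are expected to be lost over the whole year. With losses spread evenly, the treatment difference moves by about 1 point against a target of 20, and towards the null. Interviewers do not know the group, so nothing in the outcome calls themselves should make losses unequal, and the plan will describe who withdraws and why. The figure of about 3 months refers to breastfeeding of any kind, not to EBF/PBF, so q is an assumption. All of this stands, and it limits the size of the point.

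It does not rescue the rule. The reported rates are still pushed upwards, the 5% is only a forecast, and blinding the interviewer does not correct for who is missing.

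A reader might infer more than the article supports:
- **That the bias always favours the arm with more losses.** This holds where q − p is the same in both arms, as under no effect. At the design rates with q = 50%, losses of 5% control v 10% intervention shift the difference by 0.4 points against the arm that loses more.
- **That 1.1–2.1 points applies to both arms.** It applies only where the true rate is 18%.
- **That the duration analysis is corrupted too.** The plan specifies log-rank and Cox methods there and does not say that carrying forward replaces censoring.
- **That recalled dates can fill every missed 6-month call.** The calls record when breastfeeding ceased, not when exclusive or predominant feeding ended. A date before 6 months proves failure; a later date, or continued breastfeeding, does not prove EBF/PBF.

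**Conclusion.** The concern holds in limited form. This is a stated rule that gives a wrong answer for one identifiable group: mothers lost after reporting EBF/PBF at an earlier call. It overstates each arm's 6-month rate by L(q − p), and the filled-in values understate uncertainty. At the planned loss the effect on the comparison is small, about 1 point towards the null if losses and q are equal, and would not by itself undermine a 20-point difference. It becomes material if losses are larger or unequal, and the direction then cannot be known in advance.

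The sizes rest on q of 40–60%, which the article does not give, on lost mothers sharing their arm's true rate, and, for the unequal cases, on an illustrative 10% loss in one arm. The mechanism does not depend on those values; it needs only that some lost mothers would have ended EBF/PBF before month 6, which the article's own figures make very likely.

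**What to change.** Replace the carry-forward sentence before the analysis:

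1. Do not carry a positive EBF/PBF status forward to 6 or 12 months.
2. Keep mothers already known to have stopped breastfeeding as not EBF/PBF at later times.
3. Where the 6-month call is missed but a later call gives a cessation date before 6 months, classify the mother as not EBF/PBF at 6 months.
4. For the remaining missing values, use multiple imputation with arm, centre, last known feeding status and baseline covariates.
5. As a sensitivity analysis, count missing as not EBF/PBF in both arms. At the design rates with 5% lost per arm this gives 0.95 × 18% = 17.1% and 0.95 × 38% = 36.1%, a difference of 19 points.

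The cost is a change of wording, somewhat more programming and slightly lower reported rates. With about 12 losses expected across nine centres, the imputation model should be kept simple. The sample size does not change.
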